#### 10.2.1.2 Adverse Event Term

An adverse event term must be provided for each adverse event, preferably using the term as listed in the Common Terminology Criteria for Adverse Events v4.03 (CTCAE), available online at: <http://evs.nci.nih.gov/ftp1/CTCAE/About.html>

#### 10.2.1.3 Severity

Severity of each adverse event must be determined by using the Common Terminology Criteria for Adverse Events v4.03 (CTCAE) as a guideline, wherever possible. The criteria are available online at: <http://evs.nci.nih.gov/ftp1/CTCAE/About.html>

In those cases where the CTCAE criteria do not apply, severity should be coded according to the following criteria:

- 1 = Mild (awareness of sign or symptom, but easily tolerated)
- 2 = Moderate (discomfort enough to cause interference with normal daily activities)
- 3 = Severe (inability to perform normal daily activities)
- 4 = Life threatening (immediate risk of death from the reaction as it occurred)
- 5 = Fatal (the event resulted in death)

#### 10.2.1.4 Causality

The PI, or other delegated site investigator, must perform an evaluation of causality for each adverse event.

As this is a placebo-controlled trial, the evaluation of causality must be performed as if the patient is on active treatment.

Causal relationship to each trial treatment must be determined as follows:

- **None**

There is no evidence of any causal relationship.

- **Unlikely**

There is little evidence to suggest a causal relationship (e.g. because the event did not occur within a reasonable time after administration of a trial treatment). There is another reasonable explanation of the event (e.g. the patient's clinical condition, other concomitant treatments).

- **Possible**

There is some evidence to suggest a causal relationship (e.g. because the event occurs within a reasonable time after administration of a trial treatment). However, the influence of other factors may have contributed to the event (e.g. the patient's clinical condition, other concomitant treatments).

- **Probable**

There is evidence to suggest a causal relationship and the influence of other factors is unlikely.

- **Definitely**

There is clear evidence to suggest a causal relationship and other possible contributing factors can be ruled out.

### 10.2.2 Serious Adverse Events (SAEs)

All SAEs that occur between the signing of informed consent and 30 days post the last trial treatment administration (or after this date if the site investigator feels the event is related to the trial treatment) must be submitted to UCL CTC by fax within **1 business day** of observing or learning of the event, using the trial specific SAE Report. All sections on the SAE Report must be completed. If the event is **not being reported within 1 business day** to UCL CTC, the circumstances that led to this must be detailed in the SAE Report to avoid unnecessary queries.

#### 10.2.2.1 Events which do not require immediate reporting on an SAE Report

The following events do not require immediate reporting on an SAE Report for this trial, but must be recorded in the relevant section(s) of the CRF:

- disease progression\*
- disease related deaths\*

\* Investigators should take care to distinguish these from side effects of the trial drugs (e.g bleeds).

Please note that hospitalisation for elective treatment or palliative care, or problems with home carers, does not qualify as an SAE.

**All SAEs must be reported by site staff by faxing a completed SAE Report within  
1 business day of becoming aware of the event to UCL CTC  
[contact]**

## 10.2.2.3 Adverse Event Reporting Flowchart

[figure not shown]

#### 10.2.2.4 SAE Follow-Up Reports

All SAEs must be followed-up until resolution, and until there are no further queries. The PI, or other delegated site investigator, must provide follow-up SAE Reports if the SAE had not resolved at the time the initial report was submitted.

#### 10.2.2.5 SAE Processing at UCL CTC

On receipt of the SAE Report, UCL CTC will check for legibility, completeness, accuracy and consistency. Expectedness will be evaluated, to determine whether or not the case qualifies for expedited reporting, using the list of expected adverse events in the current IB for cediranib and SmPC for gefitinib.

The CI, or their delegate (e.g. a clinical member of the TMG), will be contacted to review the SAE and to perform an evaluation of causality on behalf of UCL CTC. If UCL CTC has considered expectedness difficult to determine, the CI, or their delegate, will be consulted for their opinion at this time.

UCL CTC will send line-listings of all SAEs to AstraZeneca every 3 months.

#### 10.2.2.6 Emergency unblinding of the treatment allocation

See [section 7.6](#) for details.

### 10.3 SUSARs

If the event is evaluated by either the site or UCL CTC as a Suspected Unexpected Serious Adverse Reaction (SUSAR), UCL CTC will submit a report to the MHRA and REC within 7 calendar days for fatal/life threatening events, with a follow-up report within a further 8 calendar days, and 15 calendar days for all other events. In the case of conflicting evaluations of causal relationship by the site and the UCL CTC/CI, both opinions will be reported.

UCL CTC will unblind any SUSARs before expedited reporting, if not already unblinded. See [section 7.6](#) (methods for unblinding) for details.

### 10.3.1 Informing Sites of SUSARs

UCL CTC will inform all PIs of all potential SUSARs that occur on the trial. PIs will receive a quarterly line listing which must be processed according to local requirements.

UCL CTC will forward reports regarding SUSARs that have occurred on other trials using cediranib to all PIs. These must be processed according to local requirements and filed with the IB.

## 10.4 Clinical Review

UCL CTC will provide safety information to the TMG and IDMC on a periodic basis for review. Should the outcome of the review result in upgrading/downgrading of SAEs to SUSARs and vice versa, UCL CTC will provide relevant reports to the MHRA and the REC.

## 10.5 Additional Safety Monitoring at UCL CTC

UCL CTC will also monitor safety data for any trial related events that are not considered related to the trial treatment. Should any trial procedures appear to be resulting in adverse events, the Trial Management Group will be contacted for their opinion. If it is declared necessary to review the conduct of the trial, UCL CTC will inform the MHRA and the REC as appropriate.

If UCL CTC detects a higher incidence in rare events than is stated in the IB/SmPC for the trial treatment, a report detailing the finding will be submitted to the MHRA and REC.

## 10.6 Pregnancy

If a female patient or a female partner of a male patient becomes pregnant at any point during the trial, a completed trial specific Pregnancy Report must be submitted to UCL CTC by fax within **1 business day** of learning of its occurrence. Consent to report information regarding the pregnancy must be obtained from the mother. The Pregnancy Monitoring Information Sheet and Consent Form for the partners of trial patients must be used for this purpose.

**All pregnancies must be reported by site staff by faxing a completed  
Pregnancy Report within 1 business day of becoming aware of the pregnancy  
to UCL CTC  
[contact]**

### 10.6.1 Pregnancy Follow-Up Reports

All pregnancies must be followed-up until an outcome is determined. Follow-up Pregnancy Reports must be submitted to UCL CTC by fax within **1 business day** of learning of the outcome. Reports must include an evaluation of the possible relationship of the trial treatment(s) to the pregnancy outcome.

### 10.6.2 SAEs During Pregnancy

Any SAE occurring in a pregnant patient must be reported using the trial specific SAE Report, according to SAE reporting procedures. See [section 10.2.2](#) (Serious adverse events) for details.

### 10.6.3 Pregnancy Report Processing at UCL CTC

UCL CTC will submit Pregnancy Reports to the MHRA and the REC should the pregnancy outcome meet the definition of a SUSAR. See [section 10.3](#) (SUSARs) for details.

## 10.7 Annual Safety Reports

UCL CTC will submit Annual Safety Reports to the MHRA and REC. This will commence one year from the date of CTA approval obtained for the trial. The final Annual Safety Report will be submitted in the year following trial closure. See [section 14.1](#) (End of Trial) for details.

## 11.0 Incident Reporting and Serious Breaches

### 11.1 Incident Reporting

Organisations must notify UCL CTC of all deviations from the protocol or GCP immediately. UCL CTC may require a report on the incident(s) and a form will be provided if the organisation does not have an appropriate document (e.g. Trust Incident Form for UK sites).

UCL CTC will assess all incidents to check if they meet the definition of a serious breach.

### 11.2 Serious Breaches

Systematic or persistent non-compliance by a site with GCP and/or the protocol, including failure to report SAEs occurring on trial within the specified timeframe, may be deemed a serious breach.

In cases where a potential or actual serious breach has been identified, UCL CTC will inform the MHRA within 7 calendar days of becoming aware of the breach.

Sites must have written procedures for notifying the sponsor of serious breaches (MHRA Guidance on the Notification of Serious Breaches, 2009).

UCL CTC will use an organisation's history of non-compliance to make decisions on future collaborations.

## 12.0 Trial Monitoring and oversight

Participating sites and Principal Investigators must agree to allow trial-related on-site monitoring, including Sponsor audits and regulatory inspections by providing direct access to source data/documents as required. Patients are informed of this in the patient information sheet and are asked to consent to their medical notes being reviewed by UCL CTC on the consent form.

### 12.1 On-site monitoring

The degree of on-site monitoring will be proportionate to the objective, purpose, phase, design, size, complexity, blinding, endpoints and risks associated with the trial. UCL CTC will determine the appropriate level and nature of monitoring required for the trial. Risk will be assessed on an ongoing basis and adjustments made accordingly.

Sites will be sent a letter in advance confirming that a routine monitoring visit is due, and including a list of the documents that are to be reviewed, interviews that will be conducted, planned inspections of the facilities, who will be performing the visit and when the visit will likely occur.

On-site monitoring will be conducted by the UCL CTC Trial Monitor/Trial Coordinator. The frequency and level of monitoring will be specified in the Trial Monitoring Plan, which will be kept in the Trial Master File and regularly updated in accordance with the aforementioned risk assessments. However, the following key areas will form the core of any on-site monitoring that occurs: consent; eligibility; capturing and reporting of Serious Adverse Events; capturing of trial endpoints; data queries; filing of essential documents in the Investigator Site File and/or trial-specific patient files; drug accountability.

#### Monitoring report

Following a monitoring visit, the Trial Monitor/Trial Coordinator will provide a report to the site, which will summarise the documents reviewed and a statement of findings, deviations, deficiencies, conclusions, actions taken and actions required. The Principal Investigator at each site will be responsible for ensuring that monitoring findings are addressed (this may be delegated to an appropriate member of staff).

---

## 12.2 Self-assessment monitoring

Participating sites may be requested to complete a self-assessment monitoring report periodically, at a frequency detailed in the Trial Monitoring Plan. This report may include, but is not limited to, Investigator Site File and Pharmacy File document version checklists, progress of local approval for amendments and SAE review.

Responses to self-assessment monitoring will be reviewed at the UCL CTC to identify areas of non-compliance/fraud and to indicate training needs. Findings may trigger an on-site monitoring visit.

## 12.3 Central monitoring

Sites will be requested to submit screening logs and staff delegation logs to UCL CTC on request and these will be checked for consistency and completeness.

Eligibility of all patients entered in the trial will be checked by an appropriately trained UCL CTC staff member prior to randomisation.

Data stored at UCL CTC will be checked for missing or unusual values (range checks) and checked for consistency over time. If any problems are identified data queries will be issued to the site. Sites are required to resolve any queries and update the relevant CRF as required. All changes must be initialled and dated. The amended version must be sent to UCL CTC and a copy retained at site.

Copies of the drug accountability logs will be collected at UCL CTC for all trial patients. Sites will be required to submit logs on request. A proportion of these will be monitored centrally to ensure completeness and correlation with data captured in the CRF.

Patients will be flagged using the NHS Information Centre (please see [section 8.2](#) for further details). MRI scans will be submitted to UCL CTC for retrospective review for the trial, conducted by imaging experts from University College London Hospital, led by a member of the Trial Management Group.

## 12.4 Non-Compliance/'for cause' on-site monitoring

Additional on-site monitoring visits may be scheduled where there is evidence or suspicion of non-compliance at a site with important aspect(s) of the trial protocol/GCP requirements. Sites will be

sent a letter in advance outlining the reason(s) for the visit, a list of the documents that are to be reviewed, interviews that will be conducted, planned inspections of the facilities, who will be performing the visit and when the visit will likely occur.

UCL CTC will assess whether it is appropriate for the site to continue participation in the trial and whether the incident(s) constitute a serious breach. See [section 11.0](#) (Incident Reporting and Serious Breaches) for details.

## **12.5 Oversight Committees**

### **12.5.1 Trial Management Group (TMG)**

The TMG will include the Chief Investigator, clinicians and experts from relevant specialities and DORIC trial staff from UCL CTC (see page 1). The TMG will be responsible for overseeing the trial. The group will meet regularly and will send updates to Principal Investigators (via newsletters or at Investigator meetings) and to the NCRI Brain Tumour Clinical Studies Group.

The TMG will agree protocol amendments on behalf of the PIs prior to submission to the REC and MHRA. All PIs will be kept informed of substantial amendments through their nominated responsible individuals.

### **12.5.2 Independent Trial Steering Committee (ITSC)**

The role of the ITSC is to provide overall supervision of the trial and ensure that it is conducted in accordance with GCP and the Protocol. The ITSC will review the recommendations of the Independent Data Monitoring Committee and, on consideration of this information, recommend any appropriate amendments/actions for the trial as necessary. The ITSC acts on behalf of the funder and Sponsor.

### **12.5.3 Independent Data Monitoring Committee (IDMC)**

The role of the IDMC is to provide independent advice on data and safety aspects of the trial. Meetings of the Committee will be held regularly (yearly or based on any safety considerations or lack of efficacy considerations). The IDMC is advisory to the ITSC and can recommend premature closure of the trial to the ITSC. The IDMC charter will define the specific responsibilities of the IDMC.

#### **12.5.4 Role of UCL CTC**

UCL CTC will be responsible for the day to day coordination and management of the trial and will act as custodian of the data generated in the trial (on behalf of UCL). UCL CTC is responsible for all duties relating to pharmacovigilance which are conducted in accordance with [section 10.0](#) (Pharmacovigilance).

## 13.0 Withdrawal of patients

In consenting to the trial, patients are consenting to trial treatment, assessments, follow-up and data collection.

### 13.1 Withdrawal from Trial Treatment

A patient may be withdrawn from all trial treatment whenever continued participation is no longer in the patient's best interests, but the reasons for doing so must be recorded. Reasons for discontinuing treatment may include:

- Voluntary discontinuation by the patient who is at any time free to discontinue his/her participation in the study, without prejudice to further treatment. At the time of discontinuation, the investigator should establish if the patient is willing to be followed for disease progression.
- Safety reasons as judged by the investigator and/or UCL CTC
- Severe non-compliance to protocol as judged by the investigator and/or UCL CTC
- Incorrect enrolment (i.e the patient does not meet the required inclusion/exclusion criteria) of the patient if there are safety reasons as judged by the investigator and/or UCL CTC
- Patient lost to follow-up
- Disease progression (unless, in the investigator's opinion the patient is receiving benefit from study treatment. It is not compulsory to stop trial treatment following radiological progression only. Where progression is radiologically determined only, a second confirmatory scan taken 6 weeks later should be assessed before withdrawal, to rule out pseudoprogression).
- Pregnancy
- Toxicity grade 3 or above causing an IMP treatment delay for >14 days (or >21 days if CI has permitted a 21 day treatment holiday), or any other unacceptable toxicity
- Intercurrent illness which prevents further treatment
- Patients withdrawing consent to further trial treatment
- Any alterations in the patient's condition which justifies the discontinuation of treatment in the site investigator's opinion

#### 13.1.1 Discontinuation of Trial Drugs

In addition, both trial drugs should be permanently discontinued in patients with the following conditions:

- Gastrointestinal perforation or wound dehiscence requiring medical intervention
- Serious haemorrhage, i.e., requiring medical intervention
- Severe hypertension (see [section 7.4.1.4](#) for hypertension management protocol)
- Nephrotic syndrome
- Severe arterial thromboembolic event
- If any case of RPLS occurs that is confirmed by imaging (CT or MRI), trial drugs should be immediately discontinued, in addition to any other measures to alleviate symptoms and control blood pressure
- Patients should not receive trial drugs within 2 weeks of major surgery. Where possible, trial drugs should be suspended for 2 weeks to allow clearance before major surgery.
- Interstitial lung disease (ILD)
- Severe change in liver function

In these cases patients should continue to have trial assessments for the purposes of follow-up. If a patient wishes to withdraw from trial treatment, sites should explain the importance of remaining on trial follow-up, or failing this of allowing routine follow-up data to be used for trial purposes and for allowing existing collected data to be used.

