| Severe hypertension:

Increase in diastolic pressure to $\geq 110$ mmHg or increase in systolic pressure to $\geq 180$ mmHg on 2 readings >1 hour apart | 
 
1. Temporarily stop cediranib and consider if hospitalisation is necessary.
 
2. Initiate treatment with a 2-drug combination including a calcium channel blocker licensed for use in severe hypertension, tailored to the patient's underlying conditions and previous anti-hypertension treatment.
 
3. If there is evidence of target-organ damage, intravenous therapy should be considered while continuing oral therapy.
 
4. Nitrates may adversely affect the therapeutic mechanism of action of cediranib but should be used if clinically indicated.
 
5. Restart cediranib at 1 dose lower than the starting dose when BP <140/90 mmHg. Monitor BP every 3 to 7 days until steady state is BP stabilised
 
6. If BP increases to >160/95 mmHg, temporarily stop cediranib and continue anti-hypertensive therapy under close supervision.
 
7. Restart cediranib at 2 doses lower than the starting dose when BP <140/90 mmHg. Monitor BP every week until steady state is BP stabilised.
 
8. If BP increases to >160/95 mmHg after dose reduction to 15 mg od, despite anti-hypertensive therapy, permanently stop cediranib.
 
 |

The development of hypertension in patients treated with cediranib is generally an early event, usually occurring in the first 4 weeks of treatment. In a minority of patients hypertension can also occur later in a treatment schedule.

The rigorous monitoring of BP and adherence to the hypertension management guidelines are necessary in order to achieve optimal hypertension control. Patients on prior anti-hypertension therapy may be particularly at risk of developing moderate or severe hypertension on cediranib. Therefore, patients with pre-existing hypertension or on anti-hypertension medications are likely to benefit from having their BP management optimised before starting cediranib.

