#### **7.4.1.7 Reversible posterior leukoencephalopathy syndrome**

Reversible posterior leukoencephalopathy syndrome (RPLS) is a rare syndrome affecting vascular endothelial cells in the brain that may lead to capillary leak and oedema, and was first described in 1996 (Hinchey et al. 1996). It has been associated with a number of conditions, including renal failure, hypertension, fluid retention, and the use of cytotoxic or immunosuppressive drugs. It has also been reported rarely in association with the use of VEGF inhibitors including bevacizumab and sunitinib. Cases of Magnetic Resonance Imaging (MRI)-documented RPLS have rarely been reported in patients receiving cediranib in clinical studies.

The syndrome can present in a variety of non-specific ways, including headache, seizures, lethargy, confusion, blindness and other visual and neurological disturbances. Hypertension may be present, but is not necessary for the diagnosis of RPLS. MRI is the most sensitive imaging modality to detect RPLS and is recommended in suspected cases to confirm the diagnosis. RPLS is reversible upon removal of any possible precipitating factors and control of hypertension.

Active management of hypertension according to the hypertension management guidelines in this section may be expected to reduce the incidence of RPLS. However, if any case of RPLS occurs that is confirmed by imaging (CT or MRI), cediranib should be immediately discontinued in addition to any other measures to alleviate symptoms and control blood pressure.

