### **7.4.2.2 Interstitial Lung Disease**

The emerging safety profile of the gefitinib, in non-small cell lung cancer patients, suggests an overall treatment related incidence of Interstitial Lung Disease (ILD) of 1% (Cohen et al. 2003). Almost a third of the cases of ILD have been associated with fatal outcomes. The reported incidence of gefitinib associated ILD has been around 2% in the post-marketing experience in Japan, around 0.3% in approximately 23,000 patients treated with gefitinib in a US expanded access program and about 1% in studies utilising gefitinib in the first-line treatment of NSCLC (with similar rates of ILD in both treatment and placebo groups). In the Iressa Pan Asia (IPASS) study in NSCLC, 2.6% of the gefitinib arm suffered ILD compared to 1.4% of the comparator arm (carboplatin/paclitaxel).

Patients with concurrent idiopathic pulmonary fibrosis whose condition worsens while receiving gefitinib have been observed to have an increased mortality compared to those without concurrent idiopathic pulmonary fibrosis (Naito et al. 2008).

Patients typically present with acute dyspnoea that progresses relatively rapidly and invariably requires inpatient admission. In some instances patients develop associated symptoms of cough and low-grade fever.

Chest radiographs are found to be normal in 10% of patients with ILD and therefore there should be a low threshold for the further investigation of the following:

- Patients with symptoms of progressive breathlessness, exertion (dyspnoea) +/- a persistent non-productive cough.
- Patients with an abnormal chest radiograph
- Patients who have or develop a restrictive ventilatory pattern of lung function abnormalities

Treatment with gefitinib should be ceased in all patients with a suspected diagnosis of ILD. High resolution computed tomography (HRCT) scanning is suggested as the most appropriate investigation to follow routine chest radiography. Providing that the respective patient is sufficiently stable then formal pulmonary function testing (including spirometry and gas transfer measurements) should be performed. High-dose dexamethasone therapy can be initiated at the discretion of the treating physician (Camus et al. 2004; Seto et al. 2006).

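### Section 13.1.1 stops both trial drugs permanently for severe hypertension, while Table 7, which it cites, restarts cediranib at a lower level and does not mention gefitinib/placebo

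*Protocol*

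**What the plan says.** Section 13.1.1 opens with a general rule, that "both trial drugs should be permanently discontinued in patients with the following conditions", and then gives a list. Severe hypertension is on it, with a pointer to section 7.4.1.4. Imaging-confirmed RPLS and interstitial lung disease are on it too.

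Section 7.4 handles the same three conditions one by one.

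- **Severe hypertension (7.4.1.4, Table 7, severe row).** Step 1 is "Temporarily stop cediranib and consider if hospitalisation is necessary". Step 5 is "Restart cediranib at 1 dose lower than the starting dose" once blood pressure is controlled. Step 7 restarts it two levels lower after a further rise. Only step 8 is a permanent stop, for a rise "after dose reduction to 15 mg od, despite anti-hypertensive therapy, permanently stop cediranib". No step mentions gefitinib/placebo.
- **RPLS (7.4.1.7).** Once imaging confirms the diagnosis, "cediranib should be immediately discontinued in addition to any other measures to alleviate symptoms and control blood pressure". Gefitinib/placebo is not mentioned.
- **ILD (7.4.2.2).** "Treatment with gefitinib should be ceased in all patients with a suspected diagnosis of ILD". Cediranib is not mentioned.

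Sections 7.4.1 and 7.4.2 each end with a sentence referring to section 13.1 for circumstances that require permanent discontinuation. No text ranks section 7.4 and section 13.1.1.

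**The concern.** For severe hypertension the two sections give different instructions for the same drug after the same event. One ends cediranib permanently; the other sets out how to bring it back. They also differ on gefitinib/placebo, which 13.1.1 stops and Table 7 leaves unaddressed. Sites reading different sections would treat like patients differently.

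The first stake is patient safety at the point of care. The second is consistency of the trial data. Under section 13.1.2, a patient who stops one drug continues with assessments as before, and the discontinuation assessment is done only when both drugs have stopped. That assessment includes an MRI, to be done within 10 days where possible (sections 7.7 and 8.2 f), and section 2.6.1.1 dates radiological progression by the first scan that meets the criteria. So the section followed affects exposure, the visit schedule and whether an extra scan falls due.

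The conflict is likely to be met in practice. Section 2.3.1 lists hypertension among the common side effects of cediranib. Section 7.4.1.4 describes it as usually arising in the first 4 weeks. Section 2.4.3.1 reports it as the main dose-limiting toxicity at 45 mg cediranib in the phase I combination study.

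**Working it through.** The core of this point is textual, and the plan has no figure of its own to reproduce. Setting the sections side by side:

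| Condition | Section 7.4 | Section 13.1.1 | Where they differ |
|---|---|---|---|
| Severe hypertension | Cediranib stopped temporarily, restarted 1 then 2 levels lower, permanent stop only after a rise at 15 mg; gefitinib/placebo not mentioned | Both drugs, permanently | Restart of cediranib; gefitinib/placebo |
| RPLS, imaging-confirmed | Cediranib discontinued; gefitinib/placebo not mentioned; no restart described | Both drugs | Gefitinib/placebo only |
| ILD | Gefitinib ceased when ILD is suspected; cediranib not mentioned; no restart described | Both drugs, permanently, listed simply as ILD | Cediranib; trigger |

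**Step 1. Can both hypertension texts be followed?** No. Under 13.1.1, steps 5 to 8 of the severe row, four of its eight steps, can never be reached, because each presupposes that cediranib has been or will be restarted. Under Table 7, the 13.1.1 entry cannot apply at onset.

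**Step 2. Does a cross-reference settle it?** No. Section 7.4.1 points to 13.1, and the hypertension bullet in 13.1.1 points back to 7.4.1.4. The references are circular. Section 7.4.1 also takes hypertension and RPLS out of its general management plan and sends the reader to their own subsections, and 7.4.2 does the same for ILD. A site could reasonably treat those subsections as governing.

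**Step 3. Is stopping one drug alone a recognised pathway?** Yes. Sections 8.2 (k) and 13.1.2 both provide for it, so a site that stops only the drug named in section 7.4 is not plainly misreading the protocol.

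**Step 4. Tally.** The sections differ on which drugs stop in 3 of 3 conditions. They differ on restart in 1 of 3, severe hypertension.

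**Step 5. How many patients?**

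- RPLS: section 2.3.1 gives more than 0.1% and less than 1%. Upper end: 0.01 × 112 = 1.1 patients.
- ILD: section 7.4.2.2 gives 0.3% to 2.6% in lung cancer programmes, and section 2.3.2 gives 1.3%. With 56 patients per arm, the gefitinib arm would have 0.003 × 56 = 0.2 to 0.026 × 56 = 1.5 patients. This assumes that the rates carry over to glioblastoma.
- Together, at most 1.1 + 1.5 = 2.6, so about 0 to 3 patients.
- Severe hypertension: the protocol gives no rate, so no count is offered.

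**The case against.** The best defence is that 13.1.1 adds to section 7.4 and does not contradict it. Section 7.4.1.7 sits under cediranib toxicity and 7.4.2.2 under gefitinib toxicity, so each naturally names its own drug. Neither says that the other drug continues. Sections 7.4.1 and 7.4.2 present the circumstances in 13.1 as additional, and 13.1.1 also opens that way. For RPLS and ILD this largely stands: a site that stops both drugs breaches neither section. The ILD entries may even be successive steps, with gefitinib ceased on suspicion and both drugs stopped once ILD is established. What remains for these two is incomplete cross-referencing.

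For severe hypertension the defence fails, since a restart and a permanent stop of the same drug cannot both apply. Three points temper the conflict. Both texts stop cediranib at onset, so they part only on restart and on gefitinib/placebo. The 13.1.1 bullet cites 7.4.1.4, so it might be meant for patients who reach the end of that pathway; but it does not say so, and step 8 would still stop cediranib alone. The lead-in to 13.1.1 is not literal for every item either, since the surgery bullet describes a suspension. None of this tells a site what to do.

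Two stronger readings are tempting. A reader might infer that all three conditions conflict on restart and would be handled in opposite ways. The documents do not support that: no text describes a restart after RPLS or ILD, and the drug named in 7.4 stops under both sections. A reader might also infer a loss of power from patients losing gefitinib early. That would need a severe hypertension rate that the protocol does not give. It would also measure the cost of adopting the rule that stops both drugs, which would remain if the sections were reconciled that way.

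**Conclusion.** The point holds in a limited form. For severe hypertension, 13.1.1 and Table 7 give instructions that cannot both be followed, and nothing in the protocol says which prevails. For RPLS and ILD the defect is smaller: the handling of the companion drug, and for ILD the trigger, are not aligned between sections. On the protocol's own rates these two concern about 0 to 3 patients, if the lung cancer ILD rates carry over.

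The consequence is inconsistent drug exposure and inconsistent use of the discontinuation assessment between sites. How many patients severe hypertension would affect cannot be derived from the document. The sample size calculation is untouched. The conclusion rests on the text alone and needs no assumption about rates or effect size.

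**What to change.** The Trial Management Group, which agrees protocol amendments under section 12.5.1, should reconcile 13.1.1 with Table 7, 7.4.1.7 and 7.4.2.2. For each of the three conditions, one instruction should state:

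- the trigger, including whether suspicion or confirmation is needed for ILD;
- what happens to cediranib;
- what happens to gefitinib/placebo;
- whether restart is possible.

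A single table to which both sections refer would prevent the texts from diverging again. Which rule applies is a clinical decision, and this review proposes none.

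The cost is a protocol amendment with the approvals in section 17.4 and notification of sites. It requires no additional data and no change to the sample size.
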